### Data collection and outcome assessments

The schedule of events for ThyrAMI 2 is shown below in Table 1.

**Table 1 Tab1:** **Schedule of events for ThyrAMI 2**

	**Pre-screening**	**Baseline**			**Randomisation**	**follow-up**							
**VISIT**		**1A**	**1B**	**1C**		**2**	**3**	**4**	**5**	**6A**	**6B**	**6C**	**7**
**assessments**	**Within 24 hours of AMI**	**7 to 10 days post AMI**	**Day 0**			**Week 4 (+/− 7 days)**	**Week 8 (+/− 7 days)**	**Week 12 (+/− 7 days)**	**Week 24 (+/− 7 days)**	**Week 52 (+/− 7 days)**			**Week 53 (+/− 7 days)**
Identification and initial approach (including provision of PIS)	X												
Eligibility criteria checked	X												
Written informed consentǂ		X											
Physical examination (height ****, weight, BP, pulse)		X										X	
Venepuncture		X*				X**	X**	X**	X**			X*	
Clinical history (medical history, medication list)		X											
Questionnaires (SF12, MLWHFQ, CES-D) completed		X										X	
Safety checks (ECG, pulse oximetry and NYHA assessment		X				X	X	X	X			X	
Cardiac MRI			X							X			
EndoPat, Badimon chamber, VerifyNow and TEG analysis				X							X		
Randomisation (after written informed consent obtained) and study drug dispensation					X ***#***								
Study medication prescribed and dispensed (following LT4 dose assessment at visits 2 to 5 only)						X	X	X	X				
Study medication compliance checks						X	X	X	X			X	
Concomitant medication						X	X	X	X			X	
Adverse events						X	X	X	X			X	X
Serious adverse events						X	X	X	X			X	X

X* 20 ml blood: TSH, FT4, FT3, TPO antibodies, Total cholesterol, HDL, Triglycerides, serum BNP, endothelial markers (10 ml gel/gold tube and 10 ml EDTA/purple tube).

X** 5 ml blood: TSH, FT4, FT3 only (gel/gold tube).

Height ****: To be measured at baseline visit only (or could be self-reported if apparatus not available; for example at participant’s home).

ǂ After full discussion and answering any questions.

List of Abbreviations:

BP, blood pressure; BTF, British Thyroid Foundation; CES-D, Centre for Epidemiologic Studies Depression Scale; ECG, electrocardiogram; LT4, levothyroxine; MLWHFQ, Minnesota Living With Heart Failure Questionnaire; MRI, magnetic resonance imaging; NYHA, New York Heart Association; PIS, patient information sheet(s); SF12, short-form health survey; TEG, thromboelastography.

### Data handling and record keeping

Medical information obtained at each visit will be recorded in the subject’s medical notes or other source documentation in real time. Data will be collected and entered into a secure, validated clinical data management system (MACRO), by an authorised member of the research study team. The data management system will be 21 CRF Part 11 compliant. Data for each visit will be entered by relevant local staff at each site. The clinical data management system will be web based; allowing access to authorised staff via password protection. Data will be handled, computerised and stored in accordance with the Data Protection Act 1998. No participant identifiable data will leave the study site (CRFs will identify participants by initials, date of birth and unique patient number only). Strict confidentiality will be ensured while dealing with patient-sensitive data in accordance with the Caldicott Guardian’s recommendations (applications will be made to the relevant Caldicott Guardian for use of NHS patient data).

All study data will be held in strict confidence by the investigators/research team. Data and documents will be stored in locked cupboards. A confidential list of trial identifiers and corresponding patient identifying details will be held at site in a locked cupboard by the Principal Investigator. The quality and retention of study data will be the responsibility of the CI. All study data will be retained in accordance with the latest Directive on GCP (2005/28/EC) and local policy.

### Submission of accrual data to the United Kingdom Clinical Research Network

This study will apply for adoption to the NIHR CRN Portfolio. Accrual data will be submitted on a monthly basis, by a delegated member of staff at the Newcastle Clinical Trials Unit, in accordance with NIHR CRN guidelines.

### Statistical considerations for ThyrAMI 2

#### Sample size

Left ventricular ejection fraction (LVEF) is considered to be the strongest predictor for adverse outcomes after an acute myocardial infarction (AMI). Previous randomised trials in patients with acute myocardial infarction that showed reduced mortality and morbidity demonstrated concurrent absolute differences in LVEF of 3 percentage points or more [31,32]. Therefore, we considered this to be a feasible and clinically important difference. The sample size calculation is based on the assumption that impact of the intervention will be assessed using analysis of covariance and uses the method described by Frison and Pocock (1992) as implemented in the sampsi procedure in Stata 13 [33].

The ThyrAMI 2 study is designed with 90% power to detect an overall difference of 3% in LVEF between the two groups (3% improvement in the placebo group and 6% in the LT4 group) 12 months after AMI, at a two-sided significance level of 5%. The SD of the effect measure is estimated to be a broad 6% [34]. Using ANCOVA (differences in change in EF from baseline between placebo and LT4 taking into account variability in the baseline with correlation between baseline and follow-up of 0.75), we calculate that 47 patients would need to be enrolled in each group, allowing for a 10% drop-out.

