**Methods/Design:**

ThyrAMI 1: This will be a prospective longitudinal observational study of patients with AMI that will be followed for 24 months to study the association between thyroid status at the time of AMI (within 24 hours of diagnosis) with vascular outcomes.

ThyrAMI 2: This will be a prospective double-blinded randomised placebo-controlled trial of levothyroxine of 12 months duration in patients with AMI and SCH.

Setting: Patients will be recruited from five hospitals in the North East of England.

Participants: One hundred patients with thyroid function tests within the subclinical hypothyroid range upon admission with an AMI and no previous history of thyroid disease.

Intervention: Levothyroxine will be administered at a starting dose of 25 mcg once daily, which will be increased at intervals if needed to maintain a TSH level between 0.4 to 2.5 mU/L, versus a placebo.

Randomisation: Participants will be randomized with a computerised randomisation algorithm, stratified by type of MI (NSTEMI versus STEMI), in a 1:1 ratio to levothyroxine therapy or placebo (as container or bottle numbers), starting within 21 (+/− 7) days of AMI.

Blinding: Assignment to either the LT4 or placebo arm will be double-blinded.

Outcomes: The outcome will be the effect of levothyroxine on ventricular function, endothelial function and blood coagulability and rheology.

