### Sampling and recruitment

A feasibility analysis showed that approximately 150 patients per month are admitted to two coronary care units in the northeast. Based on our previous study, we anticipate that 10 to 17% of these patients will have SCH [18]. If 50% of these patients will consent to participate in the trial, we will complete recruitment in 12 months at 8 participants per month.

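### The 47 per group does not follow from the stated ANCOVA inputs, which give about 42 enrolled for 90% power, and the text does not say which SD the 6% is

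*Protocol article*

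**What the plan says.** All inputs are in the Sample size section for ThyrAMI 2. The trial is "designed with 90% power to detect an overall difference of 3% in LVEF between the two groups", specified as "3% improvement in the placebo group and 6% in the LT4 group", "at a two-sided significance level of 5" per cent. On variability it says: "The SD of the effect measure is estimated to be a broad 6" per cent, with a literature reference. The method is ANCOVA by the Frison–Pocock approach in Stata's sampsi, "taking into account variability in the baseline with correlation between baseline and follow-up of 0.75". The result is: "we calculate that 47 patients would need to be enrolled in each group, allowing for a 10% drop-out", which makes 94 in total.

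The Statistical analysis section specifies the matching model, with follow-up LVEF as the dependent variable, baseline LVEF as covariate and treatment as a fixed effect. The schedule of events has one cardiac MRI at baseline and one at week 52. The abstract gives the trial size as "One hundred patients with thyroid function tests within the subclinical hypothyroid range upon admission with an AMI".

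**The concern.** A calculation with every input printed should return the printed answer, and this one does not. On its own a surplus of about five patients per group would be harmless. Two things make it worth pursuing.

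First, 90% is not the power of the planned ANCOVA at the planned size, so a reader who relies on the stated pair is misinformed about the primary analysis.

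Second, the term used for the SD is loose. It follows a sentence that expresses the effect as improvement in each group, so it could mean the SD of LVEF at one time point or the SD of the change in LVEF. ANCOVA sizing takes the first and then applies the correlation. An SD of change already contains the correlation, so applying 0.75 to it as well would count the same gain twice. The two readings lie on opposite sides of 90%, and a null primary result would be interpreted differently under each.

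**Working it through.** **Inputs (Sample size section):** difference 3 points; SD 6; correlation r = 0.75; two-sided 5% (z = 1.960); power 90% (z = 1.2816); drop-out 10%. Allocation is 1:1 (Randomisation section). There is one baseline and one follow-up measure.

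**Common term.** Per-group size before any baseline adjustment:
2 × (1.960 + 1.2816)² × (6/3)² = 84.06.
This is multiplied by a variance factor that depends on the analysis.

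**Attempt to reproduce 47 with the named method.** The ANCOVA factor is 1 − r² = 1 − 0.5625 = 0.4375.
- Evaluable: 84.06 × 0.4375 = 36.8, so 37 per group.
- Enrolled: 37/0.9 = 41.1, so 42 per group (84 in total). Inflating before rounding gives 36.78/0.9 = 40.9, so 41.
- A t-based version gives 38 evaluable and 43 enrolled. A one-sided version gives 30 and 34.

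None of these comes within two patients of 47.

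**Calculations that do give 47**
- Change-score factor 2(1 − r) = 0.5: 84.06 × 0.5 = 42.03, and 42.03/0.9 = 46.7, so 47. This needs inflation before rounding. Rounding up first gives 43/0.9 = 47.8, so 48.
- ANCOVA with drop-out applied twice: 37 → 42, then 42/0.9 = 46.7, so 47. This needs rounding at each step. In one step, 36.78/0.81 = 45.4, so 46.
- ANCOVA with a correlation of about 0.705: 84.06 × (1 − 0.705²) = 42.28, and 42.28/0.9 = 46.98, so 47.

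**Power of the planned ANCOVA at 47 enrolled** (47 × 0.9 = 42.3, about 42 evaluable per group)

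*Reading A: 6 is the SD of LVEF at one time point.*
- SE = 6 × √(0.4375 × 2/42) = 0.866.
- Power = Φ(3/0.866 − 1.960) = Φ(1.504) = 0.934 (0.928 with the t distribution).
- 90% power survives until 37 (or 38 by t) of the 47 remain, which is 21% (or 19%) drop-out.

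*Reading B: 6 is the SD of change.* Assuming equal variances at baseline and follow-up:
- LVEF SD = 6/√0.5 = 8.49; residual SD = 8.49 × √0.4375 = 5.61.
- Evaluable for 90%: 84.06 × (8.49/6)² × 0.4375 = 73.6, so 74. Enrolled: 74/0.9 = 82.2, so 83 per group (166 in total).
- SE at 42 per group = 5.61 × √(2/42) = 1.225; power = Φ(3/1.225 − 1.960) = Φ(0.49) = 0.688.

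**Effect of the abstract's figure.** With 100 enrolled and 10% lost, 45 per group are evaluable. ANCOVA power is then about 94.8% under A and 71.8% under B, so the choice between 94 and 100 changes little.

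**The case against.** The strongest reply is that nothing harmful has been shown. The section names an ANCOVA sizing method and supplies an SD and a separate baseline-to-follow-up correlation. That set of inputs fits a single-time-point SD. On that reading 47 is larger than needed, the trial exceeds its 90% target, and it tolerates about twice the drop-out it allowed for. This stands, and it makes the mismatch a fault of reporting and traceability.

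Three stronger readings are tempting and not supported.

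- **That a change-score formula was used.** The match with 47 is suggestive, but double inflation and a slightly lower correlation also give 47, and the change-score match needs a particular order of rounding. Describing ANCOVA in terms of change from baseline does not settle it either, because ANCOVA of change with baseline as covariate estimates the same treatment effect as ANCOVA of follow-up.
- **That the trial is underpowered.** The 69% follows only if 6% is the SD of change. The wording allows this but does not say it, and the cited source is not at hand.
- **That the article gives three competing targets.** The recruitment forecast, "we will complete recruitment in 12 months at 8 participants per month", is a rate. 94/12 = 7.8 rounds to 8, and multiplying back to 96 creates a target the plan does not state. The abstract's hundred does differ from 94, but it may be rounding, and the section on withdrawal allows replacement while recruitment is open, so enrolment could exceed 94. The gap is editorial.

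The core point is untouched: under neither reading of the SD is 90% the power of the planned ANCOVA with 47 enrolled per group and 10% lost.

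**Conclusion.** The point holds. The stated inputs and method give 37 evaluable and about 42 enrolled per group, against the printed 47. How 47 arose cannot be determined from the text.

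The consequence depends on one undefined quantity. If 6% is the SD of LVEF at one time point, the size is conservative by about five per group and power is about 93%. If it is the SD of change, power is about 69% and 90% would need 83 enrolled per group. The first reading fits the named method better, so this should be fixed but is not a critical defect.

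The figures assume a normal approximation, one measurement at each time point, drop-out of exactly 10% and, for the second reading, equal variances at the two time points. The mismatch between 94 and 100 is real but minor.

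**What to change.** 1. Check the source cited for the 6% and state whether it is the SD of LVEF at one time point or the SD of the change.
2. If it is the single-time-point SD, either keep 47 per group (94 in total) and state about 93% power after 10% drop-out, or state 42 per group (84 in total) for 90%. Keeping 47 is simpler and leaves the recruitment plan unchanged.
3. If it is the SD of change, restate the power for 47 per group as about 69%. Whether to enlarge the trial is then a separate design decision; reaching 90% would mean 166 in total, 72 more than 94.
4. Show the variance factor and the drop-out step, so that the printed number can be reproduced and matches the ANCOVA in the Statistical analysis section.
5. Use the same total in the abstract as in the Sample size section.

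Steps 1, 2, 4 and 5, and the restated power in step 3, are text changes that need no extra patients. Only a decision to enlarge under step 3 would add recruitment.

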### Sampling and recruitment

A feasibility analysis showed that approximately 150 patients per month are admitted to two coronary care units in the northeast. Based on our previous study, we anticipate that 10 to 17% of these patients will have SCH [18]. If 50% of these patients will consent to participate in the trial, we will complete recruitment in 12 months at 8 participants per month.

### Statistical analysis

The primary analysis will be an *intention to treat* analysis of change in LVEF before and after levothyroxine therapy. The dependent variable will be LVEF at follow-up; baseline LVEF will be included as a covariate. Residual errors will be assumed to have a normal error distribution. The difference between patients randomised to LT4 and placebo will be fit as a fixed effect. Model assumptions will be checked, and if necessary, transformations of the dependent variable will be considered. A secondary *per protocol* analysis of change in LVEF before and after levothyroxine therapy will also be performed. Both primary and secondary outcomes will be measured at baseline (prior to start of the interventional medication as well as at 52 weeks (end of study). Change in secondary outcomes between the LT4 and placebo groups will be compared using analysis of covariance. Variables that are not normally distributed will be transformed prior to parametric analyses.

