#### Randomisation

Participants will be randomised using a computerised randomisation algorithm, stratified by type of MI (NSTEMI versus STEMI), in a 1:1 ratio to levothyroxine therapy or placebo (as container or bottle numbers), starting within 21 (+/− 7) days of the AMI (date of diagnosis or the date of admission to hospital, whichever is later). In addition, investigators will be unaware of allocation and will be blinded to treatment groupings. Randomisation will be administered centrally via Newcastle Clinical Trials Unit using a secure password-protected web-based system.

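### Randomisation is stratified by MI type, but the primary LVEF model as written leaves MI type out, so its interval may be slightly too wide and its test slightly conservative

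*Protocol article*

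**What the plan says.** The Randomisation section of the protocol article allocates participants "stratified by type of MI (NSTEMI versus STEMI), in a 1:1 ratio to levothyroxine therapy or placebo"; the Abstract repeats this. MI type is the only stratification factor named.

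The Statistical analysis section sets out the primary model in some detail. On outcome and covariate: "The dependent variable will be LVEF at follow-up; baseline LVEF will be included as a covariate". On treatment: "The difference between patients randomised to LT4 and placebo will be fit as a fixed effect". It adds normally distributed residual errors, a check of assumptions and a possible transformation. MI type does not appear, and no other section says that the analysis will adjust for it.

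For the secondary outcomes the section says only: "Change in secondary outcomes between the LT4 and placebo groups will be compared using analysis of covariance". It lists no covariates for these models.

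**The concern.** Stratified allocation makes the arms nearly equal in their mix of STEMI and NSTEMI. Chance imbalance in MI type therefore contributes almost nothing to the true sampling variance of the treatment estimate. A model without MI type still leaves the difference between strata in the residual and carries it into the standard error. If that difference is real after allowing for baseline LVEF, the reported standard error, interval and p-value describe a less well balanced trial than the one that was run. At stake are a nominal 5% test that in fact runs below 5%, and a little power. The trial chose MI type as its one factor to balance, so omitting it from the primary model does not match its own design.

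**Working it through.** **Inputs from the Sample size section.** The trial is "designed with 90% power to detect an overall difference of 3% in LVEF between the two groups", with two-sided alpha 0.05, SD 6, "correlation between baseline and follow-up of 0.75", and 47 enrolled per group including 10% drop-out.

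**Assumptions, not in the documents.** Partial R² is the share of follow-up LVEF variance left after baseline LVEF that MI type explains; I take 0 to 0.10 as the working range and show 0.20 as an extreme. The simulation also assumes 40% of patients in one stratum and blocks of 4.

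**The plan's own figure.** The unadjusted size per arm is 2 × [6 × (1.960 + 1.282) / 3]² = 84.06.
- ANCOVA factor 1 − 0.75² = 0.4375: 36.8, so 37, and 37 / 0.9 gives 42. This is not 47.
- Change-score factor 2 × (1 − 0.75) = 0.5: 42.03, and 42.03 / 0.9 = 46.7, so 47.

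The stated 47 thus agrees with the change-score formula and is generous for the ANCOVA that the section names. That is a separate matter; here I take 47 as given.

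**Model as written.** Analysed per arm: 47 × 0.9 = 42.3, taken as 42.
- Residual SD = 6 × √0.4375 = 3.97.
- SE = 3.97 × √(2/42) = 0.866.
- 95% half-width with 81 degrees of freedom = 1.990 × 0.866 = 1.72 points.
- Power with the SE taken at face value = Φ(3/0.866 − 1.96) = 93.4%.

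**Adding MI type.** The SE becomes 0.866 × √(1 − R²) with 80 degrees of freedom. If balance within strata is perfect, the model without MI type has type I error 2 × [1 − Φ(1.96/√(1 − R²))], which is 4.4% at R² = 0.05 and 3.9% at 0.10. On the same footing, power is:
- without MI type, Φ[(3/0.866 − 1.96)/√(1 − R²)]: 93.9% and 94.4%;
- with MI type, Φ[3/(0.866 × √(1 − R²)) − 1.96]: 94.5% and 95.5%.

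The gain is 0.6 and 1.1 percentage points.

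**Simulation.** Stratified blocked allocation, 84 analysed, 10,000 runs per setting. Monte Carlo standard error is about √(0.05 × 0.95/10,000) = 0.2 points for type I error and √(0.93 × 0.07/10,000) = 0.3 points for power. Half-widths below come from the formula; the other columns are simulated, each shown without / with MI type.

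| Partial R² | Half-width | Excess width | Type I error (%) | Power (%) | Power difference |
|---|---|---|---|---|---|
| 0 | 1.72 / 1.72 | 0% | 4.86 / 4.87 | 92.87 / 92.87 | 0.00 |
| 0.02 | 1.72 / 1.71 | 1.0% | 4.80 / 5.02 | 92.54 / 92.75 | 0.21 |
| 0.05 | 1.72 / 1.68 | 2.6% | 4.50 / 5.03 | 93.01 / 93.79 | 0.78 |
| 0.10 | 1.72 / 1.64 | 5.4% | 4.16 / 5.12 | 93.39 / 94.74 | 1.35 |
| 0.20 | 1.72 / 1.54 | 11.8% | 2.79 / 4.97 | 94.55 / 96.64 | 2.09 |

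The spread of the treatment estimate across runs barely changes: at R² = 0.10 its empirical SE is 0.833 without MI type and 0.831 with it. The mean reported SE without MI type, by contrast, is 1.728 / 1.990 = 0.868. The fault is in the reported SE, not in the estimate.

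**The case against.** The strongest reply is that this is a condensed article. A statistical analysis plan may exist, and the text does not say that baseline LVEF is the only covariate. That is fair as far as it goes: adjustment for strata is nowhere ruled out. But the section does more than name a method. It gives the outcome, the covariate, the treatment term and the error distribution, and a reader would take that as the primary model. A later document that added MI type would be changing what is written here, so the text should say so.

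A second reply is that baseline LVEF is itself measured by MRI after the infarct and may already carry most of any difference between STEMI and NSTEMI. This stands. The consequence is conditional, and at a partial R² of zero there is none.

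Three stronger readings are tempting, and the documents do not support them.
- A reader might infer that the secondary analyses also omit MI type. Their covariates are not listed at all, so this cannot be said.
- A reader might infer that the treatment estimate loses precision. Stratification has already secured that precision; the estimate varies almost equally either way.
- A reader might infer a threat to validity or to the planned power. The error is on the conservative side, and power exceeds 90% in every setting examined.

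The closed formula also slightly exaggerates the conservatism, because it assumes perfect balance among those analysed: at R² = 0.10 it gives 3.9%, against a simulated 4.2%.

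**Conclusion.** The point holds as a minor mismatch between design and analysis, confined to the primary model. For an assumed partial R² of 0 to 0.10 the interval is 0% to about 5% wider than it need be, type I error runs from about 5% down to about 4%, and roughly 0 to 1 percentage point of power is lost. At 0.20 the excess width would reach about 12%. These sizes rest on the plan's SD and correlation, on 42 analysed per arm, and on a prognostic strength for MI type that the documents do not quantify. The omission from the written model is plain; its practical effect is uncertain and at most modest. It is worth correcting because the correction is almost free.

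**What to change.** State in the Statistical analysis section that the primary ANCOVA contains treatment, baseline LVEF and MI type (STEMI or NSTEMI, as used at randomisation) as fixed effects. For each secondary ANCOVA, name the outcome's baseline value and MI type as covariates. If an analysis plan already does this, bring the two texts into line. Settle it before unblinding, so that adjustment is not chosen on sight of the results.

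The cost is one degree of freedom, from 81 to 80 with 84 analysed. If MI type turns out not to be prognostic, the expected half-width moves only from 1.7231 to 1.7234 points. The sample size need not change.
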